## Methods

This protocol is compliant with the SPIRIT 2013 guideline for study protocols [30–32], the SPIRIT 2013 checklist is in Additional file 1: Table S1.

### Design, subjects, and power analysis

We are planning a double-blind sham stimulation-controlled study with two randomized study groups. Since there were previous studies with theta-burst stimulation in schizophrenia, this is a phase II medical device study to evaluate the clinical performance of the theta-burst rTMS protocol in schizophrenia. This superiority study will compare clinical performance in terms of efficacy and safety to sham stimulation. Ninety patients meeting the DSM-V [33] criteria for schizophrenia will be enrolled in the study. Based on a recent meta-analysis on rTMS of the frontal cortex for improving negative symptoms [10], we assumed an effect size of 0.64. Using this assumption and incorporating the baseline value as a covariate, we calculated that the probability is equal to or greater than 90% (beta = 0.90) to find a significant (alpha = 0.05) difference between study groups in negative symptom improvement with this sample size (SAS PROC GLMPOWER). Patients will be assigned to the active and the sham group in a 1:1 ratio by an adaptive randomization algorithm implemented in R [34]. The algorithm took age, sex, education, and negative PANSS score into account. Patient enrolled into the study will receive sequential patient codes, while treatment (active vs. sham) will be assigned to these codes. Patients from the outpatient care of the Department of Psychiatry and Psychotherapy, Semmelweis University will be enrolled who met all the inclusion and none of the exclusion criteria. An enrollment period of 30 months is planned, therefore approximately three subjects need to be included per month to reach the target sample size. Based on the patient flow in the outpatient unit we can screen 4–5 subjects and enroll three subjects monthly. Inclusion criteria are (1) diagnosis of schizophrenia or schizoaffective disorder; (2) clinically stabilized on antipsychotic: a stable dose of antipsychotic medication for > 4 weeks; (3) age 18–55 years, and (4) presence of negative symptoms (based on PANSS): a negative subscore ≥ 16 points and one of items N1–N7 scoring ≥ 4 or two items N1–N7 scoring ≥ 3. The exclusion criteria are (1) any significant neurological illness; (2) intellectual disability; (3) history of head injury with loss of consciousness for more than 1 h; (4) history of epileptic seizures or epileptic activity on the baseline EEG (evaluated by an expert in clinical EEG and epilepsy); (5) alcohol or drug abuse within the past 3 months; (6) depressive episode or antidepressant treatment in the past 4 weeks; (7) ECT in the medical history; (8) implanted pacemaker, implanted drug pump, cochlear implant, implanted defibrillator, implanted neurostimulator or any other TMS incompatible implanted metal device; (9) skin surface is severely injured in the stimulated region of the skull; (10) sclerosis multiplex; (11) pregnancy; (12) severe sleep deprivation; (13) severe heart failure; (14) increased intracranial pressure; (15) intreated migraine; and (16) severe positive symptoms interfere with cognitive tests.

Cognitive assessments and PANSS rating by an independent (blind to treatment condition) rater will be performed on all three visits: baseline, visit 2 (day 15), and visit 3 (day 30). A follow-up visit will be scheduled 3 months after visit 3 to assess PANSS and cognitive test battery (Fig. 1).

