## Background

Schizophrenia is a major mental disorder that affects approximately 1% of the population worldwide. Social cognition impairments and negative symptoms such as blunted affect or emotional withdrawal strongly contribute to the psychosocial functioning deficits and long-term disability in schizophrenia [1]. The state-like and trait-like components of social cognition are impaired in schizophrenia [2, 3].

The effect of current antipsychotic medications on social cognition and negative symptoms is strongly limited [4]. Therefore, the significance of non-pharmacological treatments in schizophrenia, such as rTMS, is emerging. Transcranial magnetic stimulation (TMS) is a noninvasive form of brain stimulation in which a changing magnetic field is used to cause an electric current at a specific brain area through electromagnetic induction. While evidence for the efficacy of rTMS treatment in depression is solid and led to FDA approval in 2008, findings on rTMS treatment in schizophrenia are somewhat controversial. Some results show improvement, especially in facial expression recognition and social cognition applying a standard high-frequency (10 Hz) stimulation protocol on the left DLPFC [5]. Some other approaches trying to decrease negative symptoms were unsuccessful [6]. Similarly, the results of other studies applying the same standard 10 Hz stimulation protocol on the temporoparietal cortex to ameliorate auditory hallucinations were also contradictory since some studies showed positive results [7], while others failed to find evidence compared to sham stimulation [8].

Studies applying rTMS to improve negative symptoms in schizophrenia have typically targeted the dorsolateral prefrontal cortex (DLPFC), which is based on neuroimaging findings of reduced DLPFC activation in patients with negative symptoms (e.g., [9]) and emotion processing. A meta-analysis found that rTMS stimulation of the left DLPFC is more effective than sham in treating negative symptoms of schizophrenia. However, the evidence was found to be low quality [10]. The mean weighted effect size compared to sham stimulation was 0.64 (0.32–0.96; *k* = 22, total *N* = 827). Studies with younger participants showed more substantial effects than those with older participants.

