### Statistical analysis plan

The primary endpoint will be the difference in negative symptom score (sum of PANSS items N1–N7) from baseline. Restricting the analysis to the participants with complete data would lead to biased and inefficient estimates. Data imputation methods and Maximum Likelihood Estimation (MLE) are two widely accepted approaches in clinical trials, however, MLE is easier to apply. Linear Mixed Model (LMM) analysis applying maximum likelihood estimation is a good alternative to data imputations in handling missing data. Therefore, the difference between study groups (active and sham) will be analyzed by a Linear Mixed Model analysis (PROC MIXED in SAS) with the difference (relative to baseline) in negative symptom score as the dependent variable and treatment group, time (visit), and treatment-by-visit interaction as predicting (independent) variables, while baseline negative symptom score will serve as covariate [45]. An unstructured covariance matrix will be used to model within-subject effects. If the model fails to converge using the unstructured covariance matrix, the following covariance structures will be modeled in the order given: heterogeneous Toeplitz, heterogeneous compound symmetry, heterogeneous autoregressive (1), Toeplitz, compound symmetry, autoregressive (1), variance components. The first covariance structure that allows for convergence will be selected for the final model. The effects of the same predictor variables on cognitive and social cognitive outcome variables will be analyzed in the same mixed model (separately for all cognitive and social cognitive tests).

Summary statistics for the PANSS negative score (observed and change from baseline) will be presented for all visits from baseline through visit 3. For change from baseline values at each post-baseline visit, LS means, and standard errors (SE), the between-group difference in LS means with the corresponding 95% confidence interval, *p*-value, and effect size will also be presented. In addition, LS mean ± SE over time for the change from baseline values by treatment group will also be presented in line plots.

No interim analysis are planned for this investigation.

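### Age, sex and education are used in the allocation but left out of every stated model; if they predict change, the test is mildly conservative and some power is lost

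*Protocol article*

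**What the plan says.** Under Design, subjects, and power analysis, patients are assigned "in a 1:1 ratio by an adaptive randomization algorithm implemented in R", and "The algorithm took age, sex, education, and negative PANSS score into account". The type of algorithm is not described further.

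Under Statistical analysis plan, the mixed model for the primary endpoint is given term by term: "treatment group, time (visit), and treatment-by-visit interaction as predicting (independent) variables, while baseline negative symptom score will serve as covariate". For the other outcomes, "The effects of the same predictor variables on cognitive and social cognitive outcome variables will be analyzed in the same mixed model", fitted separately for each test.

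Three of the four allocation factors therefore appear in no stated model. The article mentions no re-randomisation test or other allowance for the adaptive allocation. Its power statement also uses the baseline value as the only covariate.

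**The concern.** Balancing the arms on a factor that predicts outcome reduces the true sampling variability of the treatment difference. A model without that factor leaves its contribution in the residual variance, so the reported standard error does not reflect the gain. Confidence intervals come out somewhat too wide, the actual type I error falls below the nominal 5%, and precision that the allocation could have delivered is not used.

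This would affect the primary endpoint and, because the predictors are reused, every cognitive and social cognitive outcome. It depends entirely on whether age, sex and education predict the change once baseline is in the model.

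**Working it through.** **Inputs from the article.** 90 patients, so 45 per arm at 1:1; standardised effect 0.64; alpha 0.05 (taken as two-sided; the article does not say); baseline value as the only covariate; stated power at least 90%.

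**Assumptions, not in the article.** The correlation ρ between baseline and outcome; the share R² of the variance left after baseline that age, sex and education explain together; minimisation on four dichotomised factors with a biased coin of 0.8; analysis at one time point without dropout.

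**Step 1: the plan's own power figure.** Power comes from the noncentral t distribution with noncentrality 0.64/√(1−ρ²) × √(45/2) and 87 degrees of freedom.

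- ρ = 0: noncentrality 3.04, power 85.1%
- ρ = 0.35: noncentrality 3.24, power 89.3%
- ρ = 0.38: noncentrality 3.28, power 90.1%
- ρ = 0.40: noncentrality 3.31, power 90.6%

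The stated figure is reached if ρ is about 0.38 or more. The article gives no ρ, so the figure can be neither confirmed nor refuted. It does not rely on age, sex or education.

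**Step 2: analytic effect of adjusting.** With ρ = 0.35 the effect in residual SD units is 0.64/√(1−0.35²) = 0.68. Three added covariates multiply the noncentrality by 1/√(1−R²) and leave 84 degrees of freedom. Against 89.3% with baseline alone, power becomes 89.3% at R² = 0, 90.8% at 0.05, 92.2% at 0.10 and 94.8% at 0.20. The baseline-only standard error is larger by factors of 1.00, 1.03, 1.05 and 1.12. This slightly overstates the gain, because it ignores that balanced allocation has already narrowed the baseline-only estimate.

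**Step 3: simulation with the allocation included.** 5,000 trials per setting, effect 0 or 0.68 residual SD, least squares with baseline only (planned) against baseline plus age, sex and education (adjusted).

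| R² | Planned model: mean SE / true SD of estimate (null) | Type I error, planned | Type I error, adjusted | Power, planned | Power, adjusted |
|---|---|---|---|---|---|
| 0 | 0.211 / 0.209 | 4.8% | 5.1% | 89.4% | 88.8% |
| 0.05 | 0.211 / 0.206 | 4.2% | 4.5% | 89.4% | 90.1% |
| 0.10 | 0.211 / 0.205 | 4.4% | 5.1% | 89.8% | 91.8% |
| 0.20 | 0.211 / 0.198 | 3.7% | 5.2% | 89.5% | 94.0% |

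The Monte Carlo error of a 5% rate is √(0.05 × 0.95/5000) = 0.3 points. As a check, 2Φ(−1.96 × SE/SD) with the unrounded table entries gives 4.8%, 4.5%, 4.4% and 3.7%, in line with the simulated type I errors.

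**Step 4: repeat run for small R².** A second set of 5,000 trials per setting gave planned against adjusted power of 88.7% and 88.3% at R² = 0, 89.1% and 88.8% at 0.02, 89.4% and 89.7% at 0.03, 90.0% and 90.6% at 0.05, and 89.6% and 91.6% at 0.10. The planned model's type I error was 4.6%, 5.0%, 5.1%, 4.3% and 4.4%. Below about R² = 0.03 there is nothing to gain.

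**The case against.** **The benefit is not established by the article.** It gives no R² for any of the three factors, and no reason for choosing them; wanting comparable arms is as plausible as believing them prognostic. A reader might take the Background sentence "Studies with younger participants showed more substantial effects than those with older participants" as proof that age is prognostic. It is not: it compares treatment effects between studies, so it concerns effect modification, and a main-effect covariate for age would not model that. For the cognitive tests, the dependent variable is change from baseline, which already removes stable differences in level. Whether age or education predicts change over the treatment period is not shown. All of this stands, and it makes the consequence conditional.

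**The size depends on an assumed algorithm.** The rule and the coin probability are not given, and the simulation is a single-time-point simplification of the repeated-measures model. This also stands. The type I error shortfall is close to simulation noise at small R² and is clear only near R² = 0.20.

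**The covariates could be left to an analysis plan that is not shown.** This does not stand. The article fixes the fixed effects, the covariate and the order of fallback covariance structures, so the covariate set is a stated choice.

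**Conclusion.** The mismatch between allocation factors and model is certain from the text. Its consequence is conditional: a standard error that is too large, a mildly conservative test and some lost power, to the extent that age, sex and education predict change beyond baseline.

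Under the assumed minimisation, the power change from adjusting runs from about half a point lost at R² = 0, through 0.6 to 2 points gained at 0.05 to 0.10, to 4 to 5 points gained at 0.20. The planned model's type I error is about 5%, 4.4% and 3.7% at R² of 0, 0.10 and 0.20.

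Two stronger readings are tempting and are not supported. One is that the primary test is invalid or its type I error inflated: any error is on the conservative side, and the omission does not bias the treatment estimate. The other is that the sample size claim is wrong: it rests on the baseline covariate alone, as the model does, and is attainable at ρ of about 0.38 or more. This is an efficiency and calibration point, probably modest in size.

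**What to change.** Before unblinding, prespecify age, sex and education as fixed covariates beside the baseline value in the primary mixed model and in the models for all cognitive and social cognitive outcomes. Enter age as continuous, and education as continuous if it is recorded that way. Keep the model that adjusts for the PANSS negative score alone as a sensitivity analysis.

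No new data are needed: the allocation already uses these variables, and Clinical measures lists them among the demographics collected. The cost is a change to the model statement, about three degrees of freedom (more if education is categorical), and up to about half a point of power if the factors turn out not to be prognostic.

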**Fig. 1 Fig1:**
[figure not shown]
SPIRIT figure

### TMS treatment protocol

The TBS sessions will be delivered using the Magstim Rapid2 Plus1 stimulator (Magstim Company, Ltd). The TBS parameters we adopted follow the standard TBS protocols, with 3-pulse 50-Hz bursts given every 200 ms (at 5 Hz) and an intensity of 100% active motor threshold, as measured from the right first dorsal interosseous muscle by a 700-mm figure-of-eight coil [16, 37]. An identical-looking D70 Air Film Sham Coil will be used for sham stimulation. The sham coil also generates a magnetic field, that can be sensed by the participants, but this field does not penetrate the skull. We plan to deliver 1800 stimuli to the vermis and 1800 stimuli to the left DLPFC daily in two 9.5-min-long blocks (separated by 50 min inter stimulation intervals (ISI)) for 4 weeks (altogether 20 × 2 × 1800 = 72,000 stimuli) with a 100% motor threshold [17]. We do not intend to apply strategies to improve adherence.

### Procedures to improve the blinding process

Patients, care providers, and raters will be blinded to treatment assignment, only study nurses, who generate the treatment allocation and deliver the pulses will be unblinded. Treatment allocation is generated by the aforementioned R algorithm (see the “Methods” section for further details) on a computer operated by the study nurses. The computer is password-protected and used by the study nurses exclusively. Study nurses do not participate in any other activities in the study such as efficacy assessments. All patients will be instructed that they will be treated with TBS but will be blind to the individual group assignment. The study nurse who will deliver TBS will not take part in any assessments. All efficacy outcome measures will be assessed by blinded study personnel (raters), who will not be permitted access to the treatment sessions. Patients will be instructed not to disclose any details of the treatment session with the raters, and a research assistant will monitor the whole rating period to ensure that the procedure will be blinded. We will question all patients about the group assignment at visit 3 (end of treatment visit).

### Clinical measures

The Positive and Negative Syndrome Scale (PANSS) will be administered to all patients to assess positive, negative, and general symptom severity. Everyday functioning will be measured by the Personal and Social Performance Scale (PSP) [38], while depressive symptoms will be assessed by the Calgary Depression Scale for Schizophrenia [39, 40]. Furthermore, the following demographic data will be collected from all participants: age, gender, education, job status, accommodation, family status, medications, smoking status, illness duration, schizophrenia subtype, and handedness. Since patients will be on antipsychotic medication, the mean chlorpromazine equivalent dose will be calculated [41].

### Measures of cognition and social cognition

The following tests will be performed to assess cognitive and social cognitive functioning: (1) Reading the Mind in the Eyes Test (RMET) [36]; (2) “Faux pas” test [35]; (3) Wisconsin Card Sorting Test (WCST); (4) Digit Span Forward and Backward tests; and (5) Karolinska Directed Emotional Face set of facial emotion recogniton.

In order to assess the capacity of mental state discrimination, the Revised Version of the RMET will be used [36]. The RMET presents participants with 36 black-and-white photographs of the eye region of the face, one at a time. Each photo shows the eye region of a different actor or actress. Pictures are of equal size and depict an equal number of male and female faces. Participants will be asked to choose which of four words (one target and three foils), displayed on the screen, best describes the mental state of the actor/actress. Although the RMET seems to be an emotion recognition paradigm, results from functional neuroimaging studies revealed test-related activation in brain areas related to ToM (dorsomedial prefrontal cortex and superior temporal cortex) [42]. This unique feature of the task may be due to direct instructions to attribute mental states, the application of complex social emotions, and only the presence of eye regions. The latter two factors lead to considerable ambiguity of social information that can be solved by active mentalization. A further advantage of the RMET is that numerous schizophrenia studies have applied this measure so far and confirmed that RMET is a reliable tool to detect differences in ToM between patients with schizophrenia and healthy controls [2, 23].

The Faux-pas test assesses the ability to recognize “Faux pas”: someone mistakenly saying something they should not have [35]. The test is considered an advanced test of Theory of Mind ability as it requires subtle social reasoning: one must be able to appreciate that two protagonists might have different knowledge states and also the emotional impact the statement can have on the listener. It is a well-known instrument used to evaluate theory of mind (ToM) in autism spectrum disorders or schizophrenia. The test includes 20 short stories containing incidents of faux pas. Each story is read to the individual, who is then asked questions to determine whether or not they recognized the faux pas. Understanding the mental states behind the kinds of actions presented in the Faux Pas task can be broken down into several distinct subtasks to make clear where the respondent is having trouble. The subject gets one point for each question answered correctly. As a result, the proportion of correct answers is calculated, where the maximum score ratio is 1.0. The test indicates a deficit below 0.75.

The WCST is a broadly used tool to measure executive functioning, such as concept formation, set-shifting, and flexibility [43]. In this study, a computerized, 100-card version will be used. The number of perseverative errors is the major outcome variable of the test, its minimum is 0, while it has no theoretical maximum value. Higher values indicate worse outcomes. Punishment sensitivity (P) from the reinforcement learning model of WCST will also be used as an outcome variable [26]. Its minimum value is 0 and it has no theoretical maximum value. Lower values indicate worse outcomes.

The Digit Span Forward and Backward tests require subjects to remember and rearrange short lists of numbers. These tests assess short-term memory span [43]. The outcome variable is the number of items (numbers) the participant can recall, and lower values indicate a worse outcome.

The Karolinska Directed Emotional Face set is an emotion recognition task [44], where subjects have to identify emotional expressions from photographs of 8 male and 8 female subjects. The pictures are chosen from the Karolinska Directed Emotional Face set. There are 3 photographs of each face (happy, neutral, and sad). Hit rate is the primary outcome measure, which ranges from 0 to 100%, and lower values indicate worse outcomes.

### Laboratory

Plasma levels of antipsychotic medications and their metabolites will be measured during enrollment and close-out by the Department of Laboratory Medicine (Semmelweis University) as part of routine clinical care. Plasma levels of antipsychotics and their metabolites will be measured by liquid chromatography–tandem mass spectrometry (LC–MS-MS). Samples will be stored only for 2 weeks, then they will be destroyed. All these procedures are part of routine clinical care.

### Statistical analysis plan

The primary endpoint will be the difference in negative symptom score (sum of PANSS items N1–N7) from baseline. Restricting the analysis to the participants with complete data would lead to biased and inefficient estimates. Data imputation methods and Maximum Likelihood Estimation (MLE) are two widely accepted approaches in clinical trials, however, MLE is easier to apply. Linear Mixed Model (LMM) analysis applying maximum likelihood estimation is a good alternative to data imputations in handling missing data. Therefore, the difference between study groups (active and sham) will be analyzed by a Linear Mixed Model analysis (PROC MIXED in SAS) with the difference (relative to baseline) in negative symptom score as the dependent variable and treatment group, time (visit), and treatment-by-visit interaction as predicting (independent) variables, while baseline negative symptom score will serve as covariate [45]. An unstructured covariance matrix will be used to model within-subject effects. If the model fails to converge using the unstructured covariance matrix, the following covariance structures will be modeled in the order given: heterogeneous Toeplitz, heterogeneous compound symmetry, heterogeneous autoregressive (1), Toeplitz, compound symmetry, autoregressive (1), variance components. The first covariance structure that allows for convergence will be selected for the final model. The effects of the same predictor variables on cognitive and social cognitive outcome variables will be analyzed in the same mixed model (separately for all cognitive and social cognitive tests).

Summary statistics for the PANSS negative score (observed and change from baseline) will be presented for all visits from baseline through visit 3. For change from baseline values at each post-baseline visit, LS means, and standard errors (SE), the between-group difference in LS means with the corresponding 95% confidence interval, *p*-value, and effect size will also be presented. In addition, LS mean ± SE over time for the change from baseline values by treatment group will also be presented in line plots.

No interim analysis are planned for this investigation.

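### The primary mixed model gives baseline PANSS negative score one slope for both visits; pre-specifying baseline-by-visit is an optional, near-free safeguard

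*Protocol article*

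**What the plan says.** All references are to the protocol article.

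- **Outcome** (Statistical analysis plan): "The primary endpoint will be the difference in negative symptom score (sum of PANSS items N1–N7) from baseline".
- **Fixed effects** (same section): "treatment group, time (visit), and treatment-by-visit interaction as predicting (independent) variables, while baseline negative symptom score will serve as covariate". No baseline-by-visit term is listed.
- **Covariance** (same section): "An unstructured covariance matrix will be used to model within-subject effects", with seven ordered fallback structures.
- **Missing data** (same section): "Linear Mixed Model (LMM) analysis applying maximum likelihood estimation is a good alternative to data imputations in handling missing data".
- **Results reported** (same section): "For change from baseline values at each post-baseline visit, LS means, and standard errors (SE), the between-group difference in LS means", with confidence interval, p-value and effect size. Day 30 is not named as the sole primary contrast.
- **Visits** (Design, subjects, and power analysis): PANSS rating "will be performed on all three visits: baseline, visit 2 (day 15), and visit 3 (day 30"). A follow-up comes three months later, but the planned PANSS negative summaries stop at visit 3.
- **Allocation** (same section): 1:1 and adaptive, with negative PANSS score among the balancing factors.

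The cognitive and social cognitive outcomes use the same predictors.

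**The concern.** The model is flexible by visit in every respect but one. Group means, residual variances and the residual correlation may all differ between day 15 and day 30; the association with baseline may not. Because the outcome is a change score, its slope on baseline at visit t is

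slope(t) = correlation(baseline, visit t) × SD(t)/SD(baseline) − 1.

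A common slope is right only if this quantity is equal at both visits, and the article gives no reason to expect that. Two things are at stake if it is not. Baseline variation left in the residual inflates the SE of the visit-specific contrast. And the plan relies on maximum likelihood for missing data, whose protection under missing at random assumes a correctly specified mean model.

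**Working it through.** **Inputs from the article.** 90 patients, so 45 per arm; effect size 0.64; alpha 0.05 (taken as two-sided); power at least 90% with baseline as covariate; two post-baseline visits in the treatment period.

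**The plan's own figure.** Without adjustment, 0.64 × √(45/2) = 3.036, and Φ(3.036 − 1.960) = 85.9% (85.1% with the t distribution). With baseline correlation r the 3.036 is divided by √(1 − r²), so 90% is reached just above r = 0.35 (about 0.38 with the t distribution). The article does not state r. The stated power is attainable, but only because of baseline adjustment, so the form of that adjustment matters somewhat.

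**Does one slope have to be wrong?** No. With correlations 0.80 and 0.72 and SD ratios 1.00 and 1.11, the slopes are 0.80 × 1.00 − 1 = −0.20 and 0.72 × 1.11 − 1 = −0.20. A falling correlation alone does not settle it.

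**Simulation.** Assumptions, none from the article: baseline SD 4.5; residual SD 3 at day 15 and 4 at day 30, with correlation 0.7; about 20% missing at day 30 in the dropout scenarios; four pairs of true slopes. The unstructured model was fitted by maximum likelihood with a common slope and with a slope per visit. There were 800 runs per scenario at N = 90 for the SEs, and 25 runs at N = 20,000 for bias (Monte Carlo SE about 0.01). The SE ratio is common slope over slope by visit, for the day-30 contrast.

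| True slopes (day 15, day 30) | Model SE ratio | Bias: dropout relates to baseline equally in both arms | Bias: active arm only | Bias: opposite directions by arm |
|---|---|---|---|---|
| −0.3, −0.3 | 0.990–1.003 | 0.02 | 0.01 | 0.00 |
| −0.2, −0.3 | 0.996–1.009 | 0.00 | 0.09 | 0.17 |
| −0.2, −0.4 | 1.012–1.026 | −0.01 | 0.17 | 0.32 |
| −0.1, −0.5 | 1.079–1.095 | −0.02 | 0.31 | 0.63 |

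Bias is in PANSS points, for the common-slope model. With the interaction term it lies between −0.02 and +0.02 in every cell. A harsher stress case (27% missing, stronger opposite dependence) gave 0.31, 0.61 and 1.23 for the three unequal-slope rows, so the upper end depends on how extreme a dropout mechanism is assumed.

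**Balanced allocation.** With baseline balanced and no dropout, the empirical SE ratio is 1.00 in every slope scenario. The model SE, which drives the reported interval and p-value, stays inflated by the amounts in the table.

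**Effect on power.** Starting from 90%, 1.960 + 1.282 = 3.242. A 3% larger SE gives Φ(3.242/1.03 − 1.960) = 88%; an 8.5% larger SE gives Φ(3.242/1.085 − 1.960) = 85%.

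**Steep versus mild decay.** A second simulation assumed SD 4.5 and a day-30 effect of 0.64 × 4.5 = 2.88 points. With the baseline correlation falling from 0.85 to 0.60, the SEs were 0.822 and 0.788, equivalent to 1 − (0.788/0.822)² = 8% of the sample. With a fall from 0.80 to 0.68 the SE gain was negligible and the bias about 0.11 points.

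**The case against.** The strongest case against is that nothing here is wrong as stated. A main-effect baseline covariate is an acceptable specification, and an article may leave the exact model statement to a fuller plan. That patients are on stable medication and that the two visits are about 15 days apart both argue for similar slopes. Balancing on negative PANSS also removes much of the precision loss. All of this stands as to size. It does not remove the point, because the section lists the fixed effects explicitly, including one interaction with visit, so the common slope is the natural reading.

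Three stronger readings are tempting, and the article supports none of them:

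- **Any dropout related to baseline severity biases the contrast.** It does not. If the relation is the same in both arms, baseline stays comparable among those observed and the mis-fitted slope cancels in the difference.
- **One slope must be wrong for at least one visit.** This does not follow without the SD ratios, which the article does not give.
- **The plan wastes about 8% of its sample.** That figure rests on an assumed steep fall in correlation between day 15 and day 30.

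Dropout could differ by arm. Under Withdrawal of patient from study, intolerable adverse events lead to withdrawal, and the sham field is described as not penetrating the skull. But the article does not say whether such dropout would track baseline severity.

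**Conclusion.** The point holds as a modest refinement. The model as written imposes equal baseline slopes at day 15 and day 30, an assumption that the article neither states nor supports. If the slopes differ, the cost is about 1 to 3% in model SE for moderate differences and 8 to 9% for extreme ones. Bias requires, in addition, a dropout–baseline relation that differs between arms; it is then about 0.1 to 0.3 points in moderate cases and about 0.6 in extreme ones, against an assumed effect of 2.88 points. Its sign depends on the direction of that relation. If the slopes are equal, nothing is lost by the plan as it stands.

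The sizes rest on assumed SDs, slopes and dropout patterns. The conditions under which bias appears do not depend on the exact values. Day 30 was used for the arithmetic because the simulated dropout falls there, not because the article makes it the only primary contrast.

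**What to change.** State the primary model as: change = group + visit + group × visit + baseline + baseline × visit, with the unstructured covariance and fallback list unchanged. Use the same form, each with its own baseline score, for the cognitive and social cognitive outcomes.

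The cost is one degree of freedom per additional visit, one extra term in the model statement and no new data. With equal slopes, the simulated model SE with the term was at most about 1% larger. The term should be written into the plan before unblinding, since adding it later would be a data-driven change to the primary model.
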